### Blinding

This is a single-blinded study, and the participants are not blinded to group allocation. Examination and interpretation of the study results will be achieved by investigators blinded to group allocation. Once the study is completed, a copy of the data will be extracted in a pseudonymized form for statistical analyses. The information concerning the group allocation will be added to the data set with the intervention and control groups categorized as T and C, respectively. This work is done under a camera for documentation later (by supervisors), and the complete data entry is performed with blinding of the main researchers. The randomization key (ie, document with group details) will be kept with supervisors. They will provide the randomization key to the researchers once blinded interpretation of the results is finalized.

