## Methods

### Trial Design

This study is designed as a multicenter, investigator-blinded, parallel, 3-month, pragmatic, 2-arm, superiority (provision of PPC with usual care is superior to usual care only) RCT, in which different units from multiple hospitals are stratified and randomized. Randomization will be performed as block randomization with 1:1 allocation, and it will be conducted according to the Consolidated Standards of Reporting Trials (CONSORT) guidelines. The CONSORT statement is a guideline designed to improve the transparency and quality of the reporting of randomized trials [49,50].

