The start of the study will involve preparation of formal and essential approvals through the academic professor (HJ) responsible for the CNEU at the Faculty of Nursing and coordination with the Babylon Health Department, to obtain official agreements for sample collection according to the study criteria. The candidate envelopes will be opened and the candidates will be entered in an Excel spreadsheet. The information entered in each form will be added in sequence, and the Excel spreadsheet will be backed up, printed, and kept in a safe and secure location. A copy of the spreadsheet will be sent via email to the main investigator to contact the participants via their provided email addresses or phone numbers (Telegram, Viber, or WhatsApp). The enrollment process is outlined in Figure 1. If candidates are eligible and willing to participate, the informed consent form will be signed and the main investigator will contact each participant and send a link to the web-based baseline questionnaire via email or social communication apps (Telegram, Viber, or WhatsApp). Then, randomization will be performed via a web-based randomization system (see the randomization section).

Participants can return the signed informed consent form in a prestamped envelope provided by the unit or can take a picture of the signed consent form and send it via a text message to the main investigator. Subsequently, the main investigator will contact the participants, inform them about the results of the random distribution, and provide instructions according to the group that was randomly chosen (control or intervention group). All instructions will be completed on the phone or via text message, and participants will receive a link to a website from the main investigator (Multimedia Appendix 7), which provides all instructions and details of participation in the training course (also presented in Arabic).

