Each participant in the intervention group will complete all 9 modules of the ELNEC-PPC training course. Meanwhile, the main investigator will follow-up with the participants entering the website link and ask them via an instant message or email about the completion of steps and upload of a screenshot for each module to a Google Form URL provide to them.

After 2 weeks, the main investigator will make sure that all participants in the intervention group have completed the tasks assigned to them during the course, by asking the participants via an instant message or email, and will also send certificates for each module. Then, the electronic questionnaire (Arabic NoMAD) will be sent again to be filled out for the second time by the intervention group, and the main investigator will make sure that all the forms have been completed within 2 weeks after the training course. After that, the participants will be monitored at their workplaces for 3 months in order to measure the impact of the training course on their work and the changes that affect their roles, as well as evaluate their experiences using the NPT toolkit. Interviews will be conducted at their workplaces in the selected hospitals.

After 3 months, the main investigator will measure the variables of the interview using the NPT toolkit to create a viewpoint for PPC delivery via nurses at the end of life, and assess the modality of working in the hospital units. Simultaneously, a NoMAD link will be sent to all participants from the 2 arms for the last time to evaluate the long-term impact of the training course on providing PC.

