### Interview Procedure

Semistructured face-to-face interviews will be conducted with all nurses on successfully completing the ELNEC-PPC web-based training course. All participants have direct contact with patients, and 3 rounds of interviews will be conducted after 3 months. After consenting, participants will be interviewed by the main investigator (MA). All interviews will be audio recorded and transcribed. If participants do not want to be recorded, the main investigator will make notes and then transcribe an in-depth discussion account. Some participants will be interviewed in pairs or small groups. They will be asked about the changes they experienced in terms of care after the training. Throughout the interview rounds, participants will be questioned about the most important developments since the start of the program. They will be asked to disclose their opinions around PPC and to clarify the degree to which they would be implementing the method. Themes are based on the NPT [59] and will be reviewed to include problems from the initial meetings. This will assist researchers in exploring participant views on the simplest models of care.

Consequently, the interactive NPT toolkit will be used. It contains 16 questions for thinking through an implementation problem. The embedding will be improved, and statements and explanations will be edited for a web-enabled tool.

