The Arabic NoMAD scale consists of 31 Likert-type items. The items in section B are rated on a 10-point Likert-type scale from “not at all” to “completely.” The items in section C are rated on a 5-point Likert-type scale from “disagree strongly” to “agree strongly.” “Neutral” and “not applicable” are also assumed as choices to explain respondents’ experiences of using the intervention within the workplace (Multimedia Appendix 9). A total of 30 participants have completed the Arabic NoMAD survey, with a 100% reply rate. Content validity computed for the Arabic NoMAD scale (content validity index [CVI]) was 0.91, which is significantly higher than the suggested level of 0.80, and the item-CVI was 0.71-1.00. Scale reliability was also strong, with a Cronbach α coefficient of .77-.86 in the postcourse analysis. In a recent study, the NoMAD instrument demonstrated an indoor consistency score (α coefficient) of .76-.83 [61], and therefore, it may be considered as reliable.

The NoMAD questionnaire has been translated into 7 languages [62]. The Arabic NoMAD instrument provides a versatile “bank of items” [63], with a focus on wide item versions, for instance, to supply more anticipatory assessments. The NoMAD designers propose that the tool must be examined as a “pragmatic measure” of an intervention [64,65], and it motivates adaptation for multipurpose functions in particular application studies and meets clinical practice requirements.

The Arabic NoMAD instrument has 4 building item groups, according to reliability and validity data. In addition, there is no proposal for definite scoring instructions or construct procedures, which should be used in each study.

The time to complete the baseline questionnaire is approximately 20-25 minutes. The follow-up questionnaires are shorter, and the time to complete these is approximately 20 minutes.

At the starting point and 2-week and 3-month follow-ups, participants will be sent an email with a link that directs them to complete the Arabic NoMAD questionnaire. To ensure as high a response rate as possible in the follow-up questionnaires, several reminder emails will be sent (every 3 days). If no response is received, the investigator will attempt to communicate with the participant via text message or phone call and inquire if the participant is ready to reply to the survey over the telephone.

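### The trial is called investigator-blinded, but the analysis data set shows which arm is which and the main investigator knows the allocation

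*Protocol article*

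**What the plan says.** **What is claimed.** The Trial Design section describes a "multicenter, investigator-blinded, parallel, 3-month, pragmatic, 2-arm, superiority" trial. The Blinding section says "This is a single-blinded study, and the participants are not blinded to group allocation". It then states that the results will be examined and interpreted by people unaware of allocation, that the main researchers are blinded during data entry, and that supervisors release the randomization key only after blinded interpretation is final.

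**How the data are labelled.** Allocation is added to the pseudonymized data set "with the intervention and control groups categorized as T and C, respectively". The Randomization section already uses T for the intervention forms and C for the control forms.

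**What the main investigator does.** Under Screening for Eligibility and Enrollment, "the main investigator will contact the participants, inform them about the results of the random distribution" and then gives instructions by group. Under Process of Implementation, the same person follows module completion in the intervention group and sends the certificates. Under Interview Procedure, which concerns nurses who completed the course, "participants will be interviewed by the main investigator".

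**What happens at 3 months.** Process of Implementation has the main investigator interview with the NPT toolkit, and adds: "Simultaneously, a NoMAD link will be sent to all participants from the 2 arms". The Statistical Analysis section makes the between-group NoMAD difference at 3 months the primary comparison. For questionnaires still missing after reminder emails, the NoMAD Instrument section says "the investigator will attempt to communicate with the participant via text message or phone call and inquire if the participant is ready to reply" by telephone.

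**The concern.** A blinded analysis protects against choices that favour one arm: how items are scored, how missing answers are handled, which model is reported. The article itself says that no definite NoMAD scoring rule is proposed, so there is room for such choices. The protection is lost if the analyst can see which group is which.

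The label also tells a reader that investigators who meet participants do not know the arms. Here the primary outcome is self-reported by unblinded nurses on the four NPT constructs. The person who ran their course may discuss those constructs with them face to face at about the time they answer. If that contact moves answers in one arm and not the other, the shift enters the primary estimate directly and cannot be separated from a training effect.

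**Working it through.** The plan states no figure for this point, so the check is mainly a comparison of sections.

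1. **Does withholding the key blind the analysis?** The Blinding section says analysts lack the key. The same section puts an arm column in their data and says what its two letters mean; the Randomization section gives the same meaning. The key may still hide which named nurse owns which record, but it does not hide which group was trained. The stated procedure does not deliver blinded interpretation.

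2. **Is the main investigator blinded?** Telling nurses their arm, instructing them by group, checking course completion and interviewing course completers all require or reveal allocation. No section gives these tasks to anyone else. This conflicts with the Trial Design label and with the statement that the main researchers are blinded at data entry.

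3. **Does the contact fall on the primary measurement?** The interviews and the last NoMAD link both come at 3 months and are described as simultaneous. Interview themes are based on the NPT, and the 20 items of NoMAD section C measure the NPT constructs. Nothing says which comes first.

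4. **How much could a differential shift matter? (assumed values)** The only input from the plan is 86 per arm (Sample Size section). Assume no true effect, a simple two-sample *t* test at two-sided 5%, and a shift of *b* SD in one arm relative to the other.

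SE = sqrt(1/86 + 1/86) = sqrt(2/86) = 0.1525 SD; noncentrality = *b*/0.1525; 170 degrees of freedom.

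| Assumed shift *b* (SD) | *b*/SE | Probability of rejection |
|---|---|---|
| 0 | 0 | 5% |
| 0.1 | 0.656 | 10.0% |
| 0.2 | 1.311 | 25.6% |
| 0.3 | 1.967 | 49.9% |

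A normal approximation agrees for the first shift: P(|Z + 0.656| > 1.96) is about 0.10. These rows show sensitivity to a bias; they do not estimate one. Nor can the shift be expressed as a share of the design effect, because the Sample Size section states none. An assumed standardized difference of 0.5 at 90% power needs 85.03, so 86 per arm, which fits the plan but is not stated there.

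**The case against.** The strongest reply is that the Blinding section ties blinding to data entry, examination and interpretation, says openly that participants are unblinded, and does not say that staff in contact with nurses are blind. The Discussion also lists participant awareness and reliance on self-report as limitations. This stands in part: the article does not claim to control every bias, and social desirability in an unblinded self-report is largely a disclosed weakness. It does not rescue the T and C labels, which defeat the narrower claim too, and the limitations do not mention the investigator's own knowledge.

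Several stronger readings are tempting and are not supported:

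- **That no control nurse is interviewed.** Interview Procedure points to course completers. The Interviews section under Data Collection refers to all nurse participants, though for the purpose of judging course success. The interview is a secondary outcome, and secondary outcomes are to be analysed much like the primary. Interviews centred on the trained arm are the likelier reading, not a certainty.
- **That the main investigator telephones non-responders.** The text says only the investigator. Identity is probable, since the main investigator sends the links. The contact is a last step after emails every 3 days, may be by text, and applies to both arms.
- **That the bias favours the intervention.** Interviews about implementation problems could also prompt more critical ratings, and a caller's influence could act on both arms.
- **That every trained nurse is primed.** Some may answer NoMAD first. The defect is that the order is left open.

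**Conclusion.** The point holds in two parts and carries one secondary risk. First, the arm labels defeat the blinded analysis that the Blinding section describes. Second, the main investigator's duties contradict the investigator-blinded label. Both follow from the text without any assumption.

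The secondary risk is the unfixed order of interview and NoMAD at 3 months, together with telephone completion by someone who probably knows the arm. It is unquantified: the documents give neither its direction nor its size. The 10%, 26% and 50% error rates rest wholly on assumed differential shifts of 0.1, 0.2 and 0.3 SD in a simple two-group test, and should not be read as this trial's actual error rate. The point does not affect the sample size or the random allocation. It should be corrected because the design lacks a property that it claims, and because a cheap change removes an avoidable risk at the primary time point.

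**What to change.** - Have the supervisors recode the arms to randomly assigned neutral labels (A/B) before any data are released for analysis.
- Have the analysis and its blinded interpretation done by existing team members who had no role in allocation or participant contact. Recoding alone cannot blind a main investigator who already knows the arms. CNEU staff are not clearly suitable, since the article places randomization and participant selection with them.
- Keep the Blinding section's rule that unmasking follows final blinded interpretation.
- Replace investigator-blinded with open-label with blinded data analysis, and state that the main investigator is not blinded.
- Require the 3-month NoMAD to be submitted before any interview or NPT toolkit session.
- Use a fixed script for telephone answers, record the mode of completion, and add a sensitivity analysis without telephone responses.

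The cost is protocol wording, one recoding step, one extra data field and a small scheduling constraint at 3 months. The downside is a weaker blinding claim. No added participants are needed.

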### Interventions

Labeling will be performed according to the SPIRIT (Standard Protocol Items: Recommendations for Interventional Trials) recommendations [54] and CONSORT EHEALTH extension [55].

#### Usual Care

Participant nurses deliver usual care according to their roles appropriate for neonates, infants, toddlers, preschoolers, school-age children, and adolescents in the selected units of perinatal, neonatal, and pediatric settings. It comprises all treatment management procedures, diagnostic procedures, and referral processes, which are considered relevant in terms of case history, clinical results, and practical everyday practice. After trial completion, participants in this group will be allowed to access a web-based training course similar to that provided in the intervention group.

#### PPC With Usual Care

The online ELNEC-PPC course is being developed in collaboration with Relias Learning Systems [56]. The ELNEC-PPC course involves complete nationwide work to advance palliative end-of-life care delivered through health care experts in perinatal, newborn, and pediatric contexts. The mission depends on the unique ELNEC care course training, which involves cooperation between “The City of Hope” and the American Association of Colleges of Nursing. This design may include a combination of investigation and knowledge in PC and is meant to help with applying evidence-based practice. The American Association of Schools of Nursing Peaceful Death: Recommended Competencies and Curricular Guidelines for End-of-Life PC and the 1997 Drug Report have been considered. The electronic training course is going to be included in modules that are for 2.5 days, and those who complete the ELNEC-PPC course will be able to take the knowledge to clinical practice [18]. The curriculum involves the following 9 modules that are specific to the care of children who have life-limiting illnesses, and their families [57]: module 1, nursing PPC introduction; module 2, perinatal and neonatal PC; module 3, PPC communication; module 4, PPC ethical/legal issues; module 5, PPC cultural and spiritual considerations; module 6, PPC pain management; module 7, management of symptoms; module 8, PPC loss, grief, and bereavement; and module 9, PPC at the time of death.

Each module will cover about 20 minutes of PowerPoint slides and data text, and 40 minutes of activity sessions for clinical application. The clinical course will comprise case management studies, film vignettes including critical thinking questions, and “stop and think” queries that require the user to answer in order to continue through the module. On the completion of each training module, the participant will be requested to reply to 10 National Council Licensure Examination–format questions to complete mastery. This interactive online course is important for all participants in the selected Hillah city hospitals.

The following 8 main themes are present within each of the modules: (1) Family as a unit of care; (2) Important role of the nurse as an advocate; (3) Cultural importance as an influence in PC; (4) Critical demand for notice to special populations like ethnic subgroups, deprived individuals, and uninsured individuals; (5) PC influence on care systems according to context; (6) Critical monetary matters impact PC; (7) PC is not limited to cancer or AIDS, and is vital in serious diseases and cases that can result in sudden death; and (8) Interdisciplinary care is vital for end-of-life care [18].

It has been hypothesized that the NPT would be a useful conceptual tool because it provides a strong analytic framework for understanding the organization and operationalization of tasks (their implementation), creating them as routine elements of lifestyle (their embedding), and sustaining embedded practices in social contexts (their integration) [28].

### Process of Implementation

Institutional review board approval will be obtained from Babylon University/Nursing Faculty and from the selected hospitals in Babil Province Health Department, where the study will take place. Informed consent will be submitted to the selected hospitals, and the nurses will be given 1 week to decide if they wish to participate. The Arabic NoMAD pretest electronic questionnaire will be provided to those nurses who decide to participate.

The intervention group will receive the ELNEC-PPC training course through the Relais Academy website. The main investigator will send a link of the e-questionnaire to all participants via their email addresses or via social media (Telegram, Viber, or WhatsApp). It includes questions that describe the experience and role of each participant in providing PPC, and within 2 weeks, each participant will return to their appropriate routine practice. The time periods from pretest (the ELNEC-PPC training intervention) to posttest will be 2 weeks and 3 months.

The main investigator will send a link of the website that provides details of participation in the training course and enrolling at Relias Academy (see link in Textbox 1). The website also provides support in Arabic to all participants in the intervention group. For enrolling at Relias Academy, the participants need to follow the process presented in Textbox 1.

Process for enrolling at Relias Academy.Go to www.reliasacademy.comSelect “Sign In” from the top right corner of the screenType in your email address and passwordEmail: Provide the emailPassword: Provide the passwordConfirm that the End-of-Life Nursing Education Consortium-Pediatric Palliative Care course you are looking for is presentOnce logged in, click on “Manage Account” and select “Courses”

Participants will login to the site from the link sent to them, and will read the steps necessary to complete the course (our website will provide the information). The site was designed for research purposes by the researchers to deliver the content of the course that was on the Relais Academy platform and provide the required survey to the participants to facilitate the process of implementation. It was created using Google Site, a service provided by Google to build websites, and the way it works is similar to the way a wiki works.

Each participant in the intervention group will complete all 9 modules of the ELNEC-PPC training course. Meanwhile, the main investigator will follow-up with the participants entering the website link and ask them via an instant message or email about the completion of steps and upload of a screenshot for each module to a Google Form URL provide to them.

After 2 weeks, the main investigator will make sure that all participants in the intervention group have completed the tasks assigned to them during the course, by asking the participants via an instant message or email, and will also send certificates for each module. Then, the electronic questionnaire (Arabic NoMAD) will be sent again to be filled out for the second time by the intervention group, and the main investigator will make sure that all the forms have been completed within 2 weeks after the training course. After that, the participants will be monitored at their workplaces for 3 months in order to measure the impact of the training course on their work and the changes that affect their roles, as well as evaluate their experiences using the NPT toolkit. Interviews will be conducted at their workplaces in the selected hospitals.

After 3 months, the main investigator will measure the variables of the interview using the NPT toolkit to create a viewpoint for PPC delivery via nurses at the end of life, and assess the modality of working in the hospital units. Simultaneously, a NoMAD link will be sent to all participants from the 2 arms for the last time to evaluate the long-term impact of the training course on providing PC.

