### Objectives

#### Primary Objective

The primary objectives are as follows: (1) to hold a short ELNEC-PPC web-based training program at selected Hillah city hospitals in Iraq by July 2020, and (2) to evaluate the impact and effectiveness of this project through the NPT at the beginning of the web-based training course, and 2 weeks and 3 months after the end of the web-based training course, define PC advocacy activities, and implement the principles found in the ELNEC-PPC web-based training program at selected Hillah city hospitals in Iraq by August 2020.

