In the CNEU, randomization will be performed. If randomized to the ELNEC-PPC web-based training course in addition to usual care (intervention group), participants will be sent a link to the website that has all instructions for enrolling and registering in the training course and assistance on how to maintain access via instant messaging or email. Moreover, participants will be given information about their follow-up assessments and how to contact the main investigator if needed. If a participant declines to participate, the main investigator will ensure that the information from the baseline questionnaire is deleted. If randomized to usual care, participants will be instructed on the principles of usual care and will be given the same information as provided to the intervention group about their follow-up assessments and how to contact the main investigator if needed. The flow of participants through the trial is described in Figure 1.

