### Outcomes

All outcomes of the study will be assessed at the starting point, and after 2 weeks and 3 months. Participant characteristics and demographic variables will be collected at baseline. Participant characteristics include age, gender, and relevant comorbidities, while demographic variables include job category, work experience, academic qualification, job title, and the number of local training courses. The outcomes are based on the recommendations of the NPT and its 4 related constructs [58].

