Repeated measures ANOVA will be performed to assess the multivariate main intervention effects (associated with controls) considering pre, post, and follow-up time points, as well as their interface effects. A 2-sided *P* value <.05 will be considered significant. The standardized effect size (Cohen *d*) will also be calculated. Mediator analysis will be controlled to determine which subgroups would benefit further from the intervention, with outcome variables regressing on independent variables, including age group, sex, education, and starting Arabic NoMAD score.

Secondary outcomes will be analyzed using an approach similar to the approach described for the primary outcome with linear mixed models for repeated measures. The data from the 2-week and 3-month follow-ups will also be analyzed using the approach described above for the primary outcome.

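### The protocol contradicts itself on whether control nurses complete the 2-week NoMAD, on which the 2-week contrast and the three-time-point ANOVA depend

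*Protocol article*

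**What the plan says.** Two sets of statements describe who completes the NoMAD and when.

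*Procedural text (Process of Implementation).* About two weeks into the study, "the electronic questionnaire (Arabic NoMAD) will be sent again to be filled out for the second time by the intervention group". For the 3-month assessment, the following paragraph says "a NoMAD link will be sent to all participants from the 2 arms for the last time". The section contains no instruction to send controls a form at 2 weeks.

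*Schedule text.* The Outcomes section says "All outcomes of the study will be assessed at the starting point, and after 2 weeks and 3 months". The NoMAD Instrument section says "At the starting point and 2-week and 3-month follow-ups, participants will be sent an email with a link". Under Screening for Eligibility and Enrollment, nurses randomized to usual care "will be given the same information as provided to the intervention group about their follow-up assessments". None of these restricts the 2-week form to one arm.

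*Analyses that use the 2-week data (Statistical Analysis).* The primary estimate is the between-group mean difference in NoMAD at 3 months, from a random-effects model over three time points using whatever data are available. A period-by-group interaction is planned, and the 2-week data are to be analysed in the same way as the primary outcome. In addition, "Repeated measures ANOVA will be performed to assess the multivariate main intervention effects (associated with controls) considering pre, post, and follow-up time points".

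*Time origin.* Process of Implementation says "The time periods from pretest (the ELNEC-PPC training intervention) to posttest will be 2 weeks and 3 months". The Primary Objective instead places the assessments at the start of the course "and 2 weeks and 3 months after the end of the web-based training course". The Abstract gives the course a length of 2 weeks.

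**The concern.** Process of Implementation is the step-by-step account that study staff would follow. It limits the second questionnaire to the trained arm and then, one paragraph later, takes care to name both arms for the last one. Staff could reasonably conclude that controls are contacted only at baseline and 3 months.

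The Statistical Analysis section relies on control data at 2 weeks. A cell that was never collected in one arm cannot be recovered by later modelling, so the short-term comparison would be lost for good.

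The time origin adds to the problem. A control nurse has no course end, so a rule that counts from the end of the course gives that nurse no date for either follow-up.

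**Working it through.** **Inputs.** 86 nurses per arm (Sample Size); three NoMAD time points (Outcomes); recipients at each time point (Process of Implementation, compared with Outcomes and NoMAD Instrument); 2-week course (Abstract).

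**The plan's own figure.** The Sample Size section gives 86 per arm for two-sided 0.05 and power 0.90 but states no effect size; its 0.5 is a correlation. Assuming a standardized difference of 0.5, a two-sample t test needs 86 per arm, which reproduces the figure. Assumed values of 0.3, 0.4 and 0.6 give 235, 133 and 60. This point uses 86 only as a head count, and nothing below depends on the assumed effect.

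**Step 1. Recipients by time point.**

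| Time | Process of Implementation | Outcomes and NoMAD Instrument |
|---|---|---|
| Baseline | both arms | both arms |
| 2 weeks | intervention only | no restriction by arm |
| 3 months | both arms | no restriction by arm |

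Planned control questionnaires: 86 × 3 = 258. Not sent under the procedural text: 86. Share: 86/258 = one third.

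**Step 2. What can be estimated.** Write T and C for the arm means, with subscripts B (baseline), 2 (2 weeks) and 3 (3 months). A contrast is estimable only if it is a combination of cell means that are observed.

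- Common-baseline model, parameters B, C2, C3, T2, T3. With all cells filled the design has rank 5 of 5. Without C2 it has rank 4 of 5.
- Separate-baseline model, six parameters. With all cells filled the rank is 6 of 6. Without C2 it is 5 of 6.

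In both models, without C2:

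- 2-week contrast T2 − C2: not estimable.
- 3-month contrast T3 − C3: estimable.
- 2-week interaction component (T2 − TB) − (C2 − CB): not estimable, because it contains C2.
- 3-month interaction component (T3 − TB) − (C3 − CB): estimable, because all four cells are observed.

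With both arms measured at 2 weeks, every one of these contrasts is estimable, and the sample size does not change.

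**Step 3. Repeated measures ANOVA.** The protocol does not say how this procedure handles missing values. In the usual complete-case form, a nurse needs all three measurements to be retained. Under the procedural text that leaves at most 86 intervention nurses and 0 of 86 controls, so no comparison with controls is possible. The mixed model does not have this problem because it uses incomplete records.

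**Step 4. Time origin.** Assume that the course starts at the pretest and lasts 2 weeks.

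- Counted from the pretest: forms at 2 weeks and 3 months. The first falls at about the end of the course.
- Counted from the end of the course: 2 + 2 = 4 weeks, and 3 months + 2 weeks after the pretest.
- Process of Implementation also lets the second form be completed up to 2 weeks after the course and only then starts 3 months of monitoring. The last form could then come as late as 2 weeks + 2 weeks + 3 months, about 4 months after the pretest.

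The last form is therefore due anywhere from 3 to about 4 months after the pretest, depending on which sentence is followed. Only the origin at the pretest gives a control nurse a date.

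**The case against.** The best defence is that one sentence stands against several. The NoMAD Instrument section is the dedicated data collection text, and it sends the link at all three time points without distinguishing the arms. Outcomes says the same, controls receive the same follow-up information, and the analysis plan presupposes 2-week data in both arms. The sentence limited to the intervention group sits in an account of how the course is delivered, where the focus is naturally on the trained nurses.

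This defence stands against three stronger readings that a reader might infer:

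- *That controls certainly have no 2-week data.* The documents do not settle this. They state both plans.
- *That the whole group-by-time interaction, or the primary result, is lost.* Even on the literal reading, controls have baseline and 3-month forms. The primary contrast is at 3 months, when both arms are expressly measured.
- *That the arms will be measured at different elapsed times.* The origins conflict, but nothing in the text rules out a common sending date for both arms.

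A reader might also bring a power argument against the ANOVA. That would need an effect size the protocol does not give, and it would have to count the ANOVA's planned interaction test as well as its main effect. It has no bearing on who receives the 2-week form.

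The defence does not remove the contradiction. Process of Implementation itself separates one arm from both arms, so shorthand is not a comfortable explanation, and it is the text that staff would work from.

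**Conclusion.** The point holds as an internal contradiction that must be reconciled. If Process of Implementation is followed, 86 of 258 planned control questionnaires are not sent, the 2-week contrast and the 2-week interaction component are not estimable, and a complete-case three-time-point ANOVA has no control arm. If Outcomes and NoMAD Instrument are followed, nothing is lost. In either case the primary 3-month contrast and the baseline-to-3-month interaction component remain estimable.

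The ANOVA result assumes complete-case handling. The estimability results assume only that an unsent form yields no data.

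The conflict over the time origin is also real, and it reaches the primary time point because it leaves the date of the last form open by about a month. The role of the ANOVA beside the mixed model is a lesser matter that one sentence can settle.

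**What to change.** 1. In Process of Implementation, state that the 2-week NoMAD goes to both arms, in agreement with Outcomes and NoMAD Instrument.
2. Replace the two time origins in the Primary Objective and Process of Implementation with one calendar schedule that applies equally to both arms, and align the Abstract. Place the 2-week form so that it still follows course completion. Simply counting 2 weeks from randomization would put it at about the end of the 2-week course and change what it measures.
3. In Statistical Analysis, state that the mixed-model contrast at 3 months is the primary analysis and that the repeated measures ANOVA is supportive.

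The cost is one extra e-questionnaire link to 86 control nurses, using the reminder procedure already planned, plus wording changes. The sample size is unaffected.
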